### Composition of the data monitoring committee, its role, and reporting structure {21a}

Since the two drugs used in this study, baricitinib and hydroxychloroquine, were all approved in China and many other countries, there is no Data Safety Monitoring Board (DSMB) committee for the safety monitoring in this study. However, this study was approved by the Institutional Review Board (IRB) of Peking Union Medical College Hospital (PUMCH) and other sites. In case of SAEs, the researchers will report to IRB and State Food and Drug Administration of China within 24 h. Moreover, since this is not a blinded study, there is no DSMB required to protect blinding of the researchers and physicians.

### Adverse event reporting and harms {22}

An adverse event (AE) is any untoward medical occurrence (including an abnormal laboratory finding), in a patient or clinical trial subject administered a medicinal product temporally associated with the use of a study agent(s), whether or not related to the study agent(s), occurring as soon as the patient has signed the informed consent form and at any time during the study. All adverse events reported by the subject or observed by the investigators will be recorded in the CRF. AEs also include an undesirable medical condition occurring, even if no study treatment has been administered.

For all AEs, the investigator will assess the causal relationship between the study drug and the AE using his/her clinical expertise and judgment according to the following algorithm that best fits the circumstances of the AE:

The investigator will interpret and document whether or not an AE has a reasonable possibility of being related to study treatment, study device, or a study procedure, taking into account the disease, concomitant treatment or pathologies. The investigator will decide whether the patient will drop out of the study due to the AEs.

A “reasonable possibility” means that there is a cause and effect relationship between the investigational product, study device, and study procedure and the AE. The investigator answers yes/no when making this assessment.

A serious AE (SAE) is any AE from this study that results in one of the following outcomes: death; initial or prolonged inpatient hospitalization; a life-threatening experience (that is, immediate risk of dying); persistent or significant disability/incapacity; congenital anomaly/birth defect; important medical events that may not be immediately life-threatening or result in death or hospitalization but may jeopardize the patient or may require intervention to prevent one of the other outcomes listed in the definition above.

Record the incidence of AEs and SAEs, especially which may cause discontinuation of the study.

Attention should be paid to monitoring the risk of serious infections such as tuberculosis, hepatitis B and other infections after medication. The risk of thromboembolic events should be monitored. Other adverse events included abnormal blood routine test, abnormal liver and kidney function test, allergic reaction, and gastrointestinal reaction.

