### Permanent discontinuation from investigational product

Investigational product must be permanently discontinued if the patient or the patient’s designee requests to discontinue investigational product.

Discontinuation of the investigational product for abnormal liver tests should be considered by the investigator when a patient meets 1 of the following conditions:ALT or AST > 8 × upper limit of normalALT or AST > 5 × upper limit of normal for more than 2 weeks after temporary interruption of investigational productALT or AST > 3 × upper limit of normal and total bilirubin level > 2 × upper limit of normalALT or AST > 3 × upper limit of normal with the appearance of fatigue, nausea, vomiting, right upper quadrant pain or tenderness, fever, rash, and/or eosinophilia (> 5%)

Investigational product should be permanently discontinued if any of the following laboratory abnormalities are observed:WBC < 1 × 10^9^ cells/LANC < 0.5 × 10^9^ cells/LALC < 0.2 × 10^9^ cells/LHgb < 6.5 g/dL

Temporary interruption rules must be followed where applicable. For laboratory values that meet permanent discontinuation thresholds, investigational product should be discontinued. However, if in the opinion of the investigator the laboratory abnormality is due to intercurrent illness such as cholelithiasis or another identified factor, laboratory tests may be repeated. Only when the laboratory value meets resumption thresholds (Table 1) following the resolution of the intercurrent illness or other identified factors may the investigator restart investigational product.

In addition, patients will be discontinued from investigational product in the following circumstances:PregnancyMalignancyDevelopment of a VTE (DVT/PE) during the study

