### Participant timeline {13}

Table 2 shows the participant timeline. The window period of each visit is 2 weeks.

**Table 2 Tab2:** The participant timeline

	− 4 weeks (screening)	0 weeks (start medication)	4 weeks	8 weeks	12 weeks (switch checkpoint)	16 weeks	20 weeks	24 weeks (the end of study)
Visit	0	1	2	3	4	5	6	7
informed consent	√							
Medical history record	√							
Vital signs	√	√	√	√	√	√	√	√
Infection screening like hepatitis and TB	√							√
complete blood cell count	√	√	√	√	√	√	√	√
Renal and liver function test	√	√	√	√	√	√	√	√
Urine routine test	√	√	√	√	√	√	√	√
Acute phase reactants (ESR, CRP)	√	√			√			√
Autoantibodies (antinuclear antibody, anti-SSA, anti-SSB, et al.)	√							√
Immunological parameters (Ig, complement, RF)	√				√			√
Exocrine gland function	√				√			√
Labial salivary gland biopsy	√							√
PGA score	√	√			√			√
ESSDAI score	√	√			√			√
ESSPRI score	√	√			√			√
Adverse events	√	√	√	√	√	√	√	√
Concomitant medication	√	√	√	√	√	√	√	√

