## Assignment of interventions: blinding

### Who will be blinded {17a}

Because this is an open-label study, all the participants and researchers will not be blinded.

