### Plans to promote participant retention and complete follow-up {18b}

The participants will receive extensive information about the study during the recruitment. The importance of completion of the follow-up will be stressed. However, the participants may voluntarily withdraw from the study for any reason at any time. We will use the application of CRDC to remind participants to follow-up regularly. They can also contact the study team if they have any questions of the study at any times.

For participants who fail to appear for study visits without stating an intention to withdraw, the study team will try to contact the participant through mobile device application, telephone calls, or short messages. If a participant withdrawal occurs for any reason, the study team must record the primary reason for a subject’s withdrawal from the study. If a participant withdraws from the study and disclosure of future information, no further evaluations will be performed, and no additional data will be collected. The investigator may retain and continue to use any data collected before such withdrawal of consent.

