### Methods in analysis to handle protocol non-adherence and any statistical methods to handle missing data {20c}

No imputation of missing data will be considered for the efficacy and analysis in this trial.

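### The adverse-event section lets an unblinded investigator take a patient out of the study, not only off drug, so the week-12 ESSDAI can be lost informatively and unequally between arms

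*Protocol article*

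**What the plan says.** Several sections of the protocol article bear on what happens to a patient after an adverse event.

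- Adverse event reporting and harms {22}: "The investigator will decide whether the patient will drop out of the study due to the AEs". No criteria are given, and continued efficacy assessment is not mentioned.
- Who will be blinded {17a}: "Because this is an open-label study, all the participants and researchers will not be blinded".
- Permanent discontinuation from investigational product: "In addition, patients will be discontinued from investigational product in the following circumstances", followed by pregnancy, malignancy and venous thromboembolism. The other rules here, and those in Table 1, HBV DNA monitoring and active TB monitoring, likewise interrupt or end the product. None says that the patient leaves the study.
- Plans to promote participant retention {18b}: "If a participant withdraws from the study and disclosure of future information, no further evaluations will be performed, and no additional data will be collected". This concerns the participant's own decision.
- Table 2 (Participant timeline {13}): ESSDAI is scored at screening and at weeks 0, 12 and 24. The visits at weeks 4 and 8 have no ESSDAI.
- Methods to handle missing data {20c}: "No imputation of missing data will be considered for the efficacy and analysis in this trial".
- Statistical methods {20a}: the only intention-to-treat sentence concerns changes at week 24, whereas the primary endpoint (Outcomes {12}) is ESSDAI response at week 12.

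**The concern.** The article distinguishes stopping the drug from leaving the study, and then, for adverse events in general, makes leaving the study the consequence. On its ordinary meaning, section {22} lets an investigator end the participation of someone who has not withdrawn consent. The decision is discretionary and made with knowledge of the arm.

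If it is made before week 12, no ESSDAI after baseline exists for that patient. No analysis plan can recover a score that was never taken, and the article rules out imputation, so the patient leaves the primary comparison.

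Unequal loss is plausible on the document's own terms. Under the eligibility criteria both arms enter after at least 12 weeks on HCQ 400 mg per day, and only one arm then starts a further drug. If adverse-event exits are more frequent in that arm and related to response, the comparison of observed response rates is biased.

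**Working it through.** **The plan's own figures.** Sample size {14} assumes response of 70% against 30%, gives 46:23 evaluable patients, and allows 20% dropout. The dropout step reproduces: 46/0.80 = 57.5, rounded up to 58; 23/0.80 = 28.75, rounded up to 29; total 87. (The 46:23 itself does not follow from 80% power: a standard two-sided, two-proportion calculation at 2:1 gives 36:18, or 42:21 with continuity correction. That is a separate matter and does not affect this point.) The 20% is not divided by cause, arm or timing.

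**Effect of selective loss.** Let p be the true response rate in an arm, x the fraction of that arm removed before week 12, and r the response rate that those patients would have had. The values of x and r are assumptions; the document gives neither.

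Observed rate = (p − x·r)/(1 − x), so bias = x(p − r)/(1 − x).

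For the baricitinib arm, with no loss among controls:

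| True p | x | r | Observed rate |
|---|---|---|---|
| 30% (no drug effect) | 10% (about 6 of 58) | 0 | 0.30/0.90 = 33.3% |
| 30% | 15% | 0 | 0.30/0.85 = 35.3% |
| 30% | 20% (about 12 of 58) | 0 | 0.30/0.80 = 37.5% |
| 70% (planned effect) | 10% | 0 | 0.70/0.90 = 77.8% |
| 70% | 20% | 30% | (0.70 − 0.06)/0.80 = 80.0% |
| 70% | 20% | 100% | (0.70 − 0.20)/0.80 = 62.5% |

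The last row reverses the bias. If r = p there is none. If both arms truly respond at 30% and both lose 10%, all non-responders, both are observed at 33.3% and no false difference arises. A spurious advantage therefore needs loss that is both related to response and unequal between arms.

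**False-positive rate.** With 30% true response in both arms, all 29 controls observed, and non-responders lost from the baricitinib arm only, the two-sided Fisher test rejects in 3.6% of trials with no loss (58:29). It rejects in 4.3% at 10% loss (52:29), 5.7% at 15% (49:29) and 7.4% at 20% (46:29).

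**What retention preserves.** If all 58:29 patients have a week-12 ESSDAI and the planned 70% and 30% hold, power is 95.7% by the normal approximation (94.3% by Fisher). Counting removed patients as non-responders instead is costly. If 20% of the baricitinib arm only is removed, independently of response, its rate becomes 0.70 × 0.80 = 56% against 30%, and power falls to 63.7%.

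**The case against.** The strongest reply is that section {22} is loosely worded and nothing in it says that data collection stops. Low blood counts, liver tests, hepatitis B and tuberculosis have their own rules, all of which end in stopping the product. This stands in part. It shows that the passages conflict, and the conflict may be one of drafting. But section {22} covers all adverse events and refers to the study, and no section says that patients off drug stay for the week-12 ESSDAI.

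A reader might infer that outcomes will certainly be lost, and only among patients doing badly on baricitinib. The document does not support that. The sentence covers both arms, no adverse-event rates by arm are given, and an adverse event is not the same as ESSDAI non-response.

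A reader might also infer that recovery of laboratory values after removal goes unobserved. Provisions for post-trial care {30} say otherwise: illness after recruitment is followed until it resolves or laboratory changes return to baseline. That is safety follow-up, however, and does not supply an ESSDAI.

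The size is open to challenge too. The 20% scenario spends the whole dropout allowance on adverse-event exits of non-responders in one arm, and at 10% the false-positive rate is still below 5%. This objection stands, and the figures are illustrations only.

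Finally, Table 2 has no early-termination visit. An article may leave that detail to the full protocol, so no weight is placed on it here.

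**Conclusion.** The point holds in a limited form. The article states a discretionary, unblinded exit from the study for adverse events that conflicts with its own drug-stopping and withdrawal rules. Together with an ESSDAI schedule that has nothing between weeks 0 and 12, and with no imputation, it can leave the primary outcome informatively missing and unequal between arms.

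The size and direction are unknown. On the assumption that 10% to 20% of the baricitinib arm is lost, all non-responders, with no control loss and no true effect, the spurious advantage is 3.3 to 7.5 percentage points. Other assumptions remove or reverse it. The text should be corrected because missing week-12 scores cannot be recovered and the change is cheap, but the point does not by itself invalidate the design.

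**What to change.** Reconcile section {22} with the interruption, discontinuation and monitoring sections and with section {18b}. State three things:

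1. Stopping or interrupting study drug because of an adverse event is not withdrawal from the study.
2. All randomised patients, on or off drug, continue the assessments already scheduled in Table 2, in particular ESSDAI at weeks 12 and 24, unless they withdraw consent.
3. The existing rules on when study drug is interrupted or stopped are unchanged.

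How patients who stopped drug count in the responder endpoint can be left to the analysis plan once their scores are collected.

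The cost is a wording amendment. The visits and assessments are already in Table 2, so nothing new has to be set up. The downside is a few more visits by patients who are off drug.

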### Frequency and plans for auditing trial conduct {23}

Periodic monitoring will be conducted independent of the investigators by monitors from the IRB and department of rheumatology in PUMCH. The independent monitor makes two on-site visits per year and checks the presence and completeness of the investigation file. The monitor checks the following data for 25% randomly picked patients: informed consents, inclusion and exclusion criteria, source data, and missing and reporting for AEs and SAEs.

### Plans for communicating important protocol amendments to relevant parties (e.g., trial participants, ethical committees) {25}

Protocol deviations will be communicated to the appropriate authorities within seven days. Amendments to the protocol will be implemented following local ethics and regulatory approvals and updated in ClinicaTrials.gov.

### Dissemination plans {31a}

Results of this research will be disclosed completely in international peer-reviewed journals. Both positive and negative results will be reported. Participants wanting to see the results of the trial can request a copy of the article from the investigators once it has been published. Full anonymity of participant’s details will be maintained throughout.

## Discussion

Baricitinib, a JAK1 and JAK2 inhibitor, was approved for the treatment of RA and widely used in many other autoimmune diseases. Baricitinib has been reported to be effective for treating cutaneous involvement in SLE, including refractory skin papulosquamous rash [25] and diffuse non-scarring alopecia [26]. The mechanism might be associated with inhibition of the IFN signaling pathway [27]. The phase 2 study of baricitinib for SLE has also shown the potential therapeutic efficacy [20]. This study also demonstrated that baricitinib treatment reduced mRNA expression of multiple IFN responsive genes and consistently suppressed two key cytokines implicated in SLE pathogenesis, IL-12p40 and IL-6 [28]. JAK inhibitors might be helpful for the treatment of pSS throughout the IFN pathway, as well as the other autoimmune diseases. But both the basic and clinical evidences are limited.

This is the first randomized controlled study to evaluate the clinical efficacy and safety of baricitinib in pSS. We have already finished the pilot study of baricitinib in active pSS patients. In the pilot study, we involved 11 pSS patients with ESSDAI ≥ 5 and treated them with baricitinib 2 mg per day on the basis of the original treatment. We found that baricitinib significantly improved the ESSDAI score and might be helpful for the management of various manifestations of pSS, such as constitutional symptoms, arthritis, skin rash, hematological involvement, and even interstitial lung disease [24]. Since it is a pilot study with no controlled group, and we did not test the dosage of 4 mg baricitinib per day in pSS, which was involved in the clinical trial of SLE [20], and proven to be effective and safe for the management of RA [29], we designed this prospective, randomized controlled study to better evaluate the potential therapeutic efficacy of baricitinib in pSS. We hope that the result of this study can provide more reliable evidence of the efficacy and safety of baricitinib in pSS. It might also lead us to explore novel therapeutic option such as other JAK inhibitors in pSS.

## Trial status

The initiation meeting of this clinical trial convened at February 12th, 2022. Screening of participants into the study with protocol Version 3.1, January 30th, 2022, began on February 12th, 2022.

## Data Availability

The datasets used and/or analyzed during the current study will be made available from the corresponding author upon reasonable request.

## Abbreviations

pSS: Primary Sjogren’s syndrome
JAK/STAT: Janus kinase/signal transduction and activator of transcription
HCQ: Hydroxychloroquine
EULAR: European League Against Rheumatism
ESSDAI: EULAR pSS disease activity index
MCII: Minimal clinically important improvement
ESSPRI: EULAR pSS patient-reported index
PGA: Physician’s Global Assessment
Th: T helper
IL: Interleukin
TGF: Transforming growth factor
GWAS: Genome-wide association study
SLE: Systemic lupus erythematosus
RA: Rheumatoid arthritis
BAFF: B-cell activating factor
IFN: Interferon
IRB: Institutional review board
ERB: Ethics review board
CRP: C-reactive protein
ESR: Erythrocyte sedimentation rate
IgG: Immunoglobulin G
RF: Rheumatoid factor
IVIg: Intravenous immunoglobulin
ALT: Alanine aminotransferase
AST: Aspartate aminotransferase
eGFR: Estimated glomerular filtration rate
WBC: White blood cell
ANC: Absolute neutrophil count
Hgb: Hemoglobin
ALC: Absolute lymphocyte count
TSH: Thyroid-stimulating hormone
VTE: Venous thromboembolism
DVT: Deep vein thrombosis
PE: Pulmonary embolism
HBV: Hepatitis B virus
HBsAg: Hepatitis B surface antigen
HBcAb: Hepatitis B core antibody
HBV DNA: Hepatitis B virus deoxyribonucleic acid
HCV: Hepatitis C virus
HCV RNA: Hepatitis C virus ribonucleic acid
HIV: Human immunodeficiency virus
TB: Tuberculosis
PPD: Purified protein derivative
GCP: Good clinical practice
PUMCH: Peking Union Medical College Hospital
HBsAb: Hepatitis B surface antibody
CRDC: Chinese Rheumatism Data Center
HIS: Hospital information system
eCRF: Electronic case report form
DSMB: Data Safety Monitoring Board
AE: Adverse event
SAE: Serious AE
